## Abstract

**Background:**

Congenital cataract is the commonest cause of preventable child blindness in the world. It affects 1: 3000 babies, 60% of whom will have bilateral disease. Although screening of the newborn red-reflex with an ophthalmoscope is recommended, there are questions over this technique's accuracy, particularly in non-specialist hands. Several studies in enriched paediatric eye clinic populations have demonstrated superior accuracy when a digital image of the the eye's reflection to infrared light is evaluated.

**Aim:**

This study uses a prototype infrared digital camera to test the hypothesis that the sensitivity and specificity of newborn screening using evaluation of the "infrared-reflex" image is superior to the standard red-reflex examination using ophthalmoscopy.

**Methods:**

140,000 newborn babies will be recruited into the study from at least 13 maternity units in England over an 18 month period. Babies will have both the standard red-reflex assessment and evaluation of the infrared-reflex using a prototype device. Since specialist gold-standard evaluation of every participant is impractical, bespoke data linkage requests to NHS England will be made. Data from the red-reflex evaluation and the presence of codes relating to cataract diagnosis and/or treatment in Hospital Episode Statistics (HES) will be retrieved for each participant a minimum of 6 months after their birth. This data will be used to calculate relative and absolute sensitivity and specificity for each screening test and comparison of accuracy using the McNemar test. Secondary outcome measures will include comparison of accuracy in different ethnic groups and screener usability scores.

**Anticipated impact:**

Confirmation of the hypothesis will support development of a commercial screening device and the possible revision of newborn screening recommendations.

**Trial registration:**

The study is registered with clinicaltrials.gov:
NCT05282147.

## Introduction

### Background and rationale

Congenital cataract is the commonest cause of avoidable childhood blindness worldwide
^
1–
3
^. Red-reflex screening for congenital cataract is recommended by the UK National Screening Committee within 72 hours of birth and at 6–8 weeks as part of the Newborn and Infant Physical Examination (NIPE). Early surgery for severe cataract is time critical, being required within the first months of life to prevent permanent visual deprivation amblyopia.

Screeners report finding red-reflex assessment difficult because of their unfamiliarity both with rare eye conditions and the technique of ophthalmoscopy
^
4
^. Additionally, darker ocular pigmentation and the baby’s pupil constriction and aversion reflexes to bright light can limit the quality of the assessment
^
5–
8
^. A national surveillance study found that only 60% of children having cataract surgery before the age of two years had been referred via the NIPE screening programme
^
9
^. Conversely, audit data record that referrals to specialist clinics for possible red-reflex abnormalities are 10 times the frequency expected for the prevalence of the condition (Public Health England audit data 2019).

Recent studies have indicated that screener evaluation of the infrared (IR)-reflex image using a prototype camera is superior in accuracy to standard red-reflex assessment in cataract enriched childhood cohorts
^
10,
11
^. If confirmed in a population screening setting, a more accurate test could minimise the number of babies with cataract whose diagnosis is delayed due to a false negative assessment and reduce the number of unnecessary false positive referrals to specialist clinics and the parental anxiety that causes.

The aim of this study is to confirm or refute the hypothesis that the sensitivity and specificity of screening with IR digital imaging using the neocam prototype device is superior to the standard ophthalmoscopic red-reflex test. This study will provide data for a subsequent health economic analysis to establish if replacing the standard method of screening with IR digital imaging would be cost effective in terms of health outcomes and reduction in unnecessary referrals.

### Review of existing evidence

IR imaging is commonly used in ophthalmology, an advantage being the avoidance of the pupil constriction and aversion response which accompanies flash photography. Additionally, the IR-reflex from the ocular fundus is monochrome, removing the issue of colour variability with ethnic pigmentation which can make evaluation of red-reflex more difficult
^
6
^. IR photoscreeners are used to detect refractive error and cataract in young children but are not practical for newborn screening because they require visual fixation and a test distance of 1 metre. In 2018, a modified smartphone (Catcam prototype) fitted with co-axial IR illumination was developed for this purpose by the study lead. Two separate proof-of-concept studies (one in Cambridge, the other in Tanzania), confirmed superior accuracy of non-specialist evaluation of the IR-reflex to red-reflex in enriched child clinic populations. With this evidence, the neocam prototype version 1 was developed by a prototyping company 42 Tech Ltd (St Ives, Cambs, UK). This neocam prototype has since been used in over 50,000 children in a large study run by the London School of Hygiene and Tropical Medicine study in Tanzania, Malawi and Uganda.

### The study device

The neocam version 2 prototype is a modified and upcycled version 1 device. It is a hand-held battery powered device, similar in size, weight and appearance to a barcode scanner (
Figure 1a&b). The device is robust and designed to be used in UK normal indoor ambient lighting conditions. Components include an integrated digital camera capturing images illuminated by its co-axial IR LED from a viewing distance of 30cm. An LCD enables data input, real-time view finding and image evaluation. Version 2 includes software and hardware modifications to improve optical resolution and user interface improvements outsourced to Keeler Ltd, (Windsor UK) by the legal manufacturer, Cambridge University Hospitals NHS Trust. The technical file and Investigator Brochure has been submitted to the Medicines and Healthcare Regulatory Authority for approval to be used in this investigation. There is no intention for the current prototype to be commercialised, although a future commercial device will be developed if the study hypothesis is confirmed.

**Figure 1. f1:**
[figure not shown]
**a**) Neocam in use – the bright infrared-reflexes are clearly visible in this infant
**b**) Neocam in use on a newborn baby.

## Objectives and outcome measures

### Primary objective

To estimate and compare the sensitivity and specificity of screening evaluation with the standard test to the intervention digital imaging test in newborn babies.

### Secondary objectives

Comparison of accuracy between tests with respect to ethnicity, comparison of accuracy between tests with respect to screener experience and usability feedback and test preference.

### Primary outcome measure

The primary outcome measures are:

 Screener evaluation “normal” or “abnormality suspected” of each eye using the standard test.Screener’s evaluation “normal” or “abnormality suspected” of each eye using the neocam digital imaging test.The gold standard evaluation (provided by data linkage +/- expert image review)

### Secondary outcome measure

Quantitative usability feedback and test preference using a screener questionnaire
^
12
^.

## Protocol

### Study design

This will be a multi-centre, prospective population-based superiority study. All participants will have both the existing standard test and the intervention test (digital imaging with the neocam device) once only within 72 hours of birth. Evaluations of each test will be compared to the gold-standard.

### Study participants and setting

All newborn babies in maternity units who are eligible for the newborn physical examination. The imaging intervention can be undertaken in the cot or in the mother’s arms.

### Recruitment (see flow chart
Figure 2)

**Figure 2. f2:**
[figure not shown]
Study flow chart.

Recruitment will take place over at least 18 months in at least 13 large maternity units. Site participation will be prioritised in maternity units with over 4000 births per year and with a diverse ethnic population.

### Enrolment

Parents will be encouraged to enrol from the 20
^th^ week of pregnancy up until discharge from the maternity unit. Posters and leaflets with a QR code will signpost parents to the
study website. Here, the parent will find information about congenital cataract and a short introductory video. The website also hosts patient information leaflets (PIS) in six languages.

The parent is asked to check that they meet several criteria for enrolment:

They are 16 or overThey are 19 weeks or more into their pregnancy or within 72 hours post-partumThey are booked into a participating maternity unit (visible in a drop-down list)

If all criteria are met, a web-button transfers them to the enrolment form in the bespoke secure study database (designed by Sealed Envelope Ltd.).

### e-consent

The negligible risk from study participation enables the use of self-directed informed e-consent. The parent enters their name, NHS number, email address and maternity unit and electronically signs a General Data Protection Regulation (GDPR) statement for this data to be securely retained. A software algorithm checks validity of the maternal NHS number to mitigate against data entry error. After checking that the parent has read and understood the PIS, the parent’s electronic signature is requested on the consent form (eICF). An automated confirmation email with eICF attachment, links to the ePIS and to contact information of the local and central research team are sent to the parent’s email address. Parents will be unable to self-enrol if they do not have an email address. They are advised to seek assistance from their local research team, who can use a hospital device and site NHS email address to complete and print documents with the parent. Following birth, the research team will search the study database for the maternal NHS number to check a copy of the eICF is present. If not, the parent will be invited to enrol and consent at this stage.

### Registration

Once the eICF is documented in the maternal database record, verbal assent is sought prior to digital imaging. The process of the baby’s registration into the study occurs when the clinician inputs the site and user code, maternal NHS number, baby’s NHS number and date of birth (DOB) into the neocam digital imaging device. A software algorithm checks validity of the maternal and baby NHS number to mitigate against data entry error.

### The intervention

After registration, the neocam device is used to image the IR-reflex in each eye. This procedure will be undertaken by a screener who has attended site training, but NIPE and Good Clinical Practice (GCP) certification is not obligatory. The imaging should take place in in either the cot or in the parent’s arms in a normally lit room.

The IR LED illuminates automatically after each eye is selected on the device display. The screener visualises the eye through the device display and aligns a visible ring calliper on the display with the corneal limbus of each eye to promote imaging at an optimal distance. The screener first evaluates the quality of the image (for movement blur and eye closure) and retakes the image if necessary. Imaging will generally take less than 2 minutes in total. Subsequently the screener evaluates each image as “normal” or “abnormality suspected” on the keypad when prompted by the device user interface. This evaluation is stored in the image file name. This ends the baby’s active participation in the study.

### Acquisition of the intervention data

Images from the neocam device are uploaded daily by connecting the device with a Trust computer via a USB cable. The images are copied to the secure study database linked by the maternal NHS number to create the electronic case report form (eCRF). More than one eCRF can be registered under the same maternal record (for instance for multiple births). The images are then deleted from the device itself. In addition to the images, the information uploaded to study database includes: site and user-role code, maternal NHS number, baby’s NHS number, baby’s DOB, date of imaging and the infrared-reflex evaluation for each eye.

### Acquisition of the standard screening data

Red-reflex screening results are routinely inputted into the nationwide Smart4NIPE (S4N) web-based database controlled by NHSE. This data includes the baby’s NHS number, DOB sex, ethnicity, screener role and red-reflex evaluation codes. This data will be retrieved through bespoke data linkage with NHSE records. Any babies with “abnormality suspected” evaluations on their standard screening tests will have this documented in the study database after both screening tests have been completed.

### Acquisition of the gold-standard data (see data linkage
Figure 3)

**Figure 3. f3:**
[figure not shown]
Data linkage chart. Abbreviations: CI: Chief investigator, HES: Hospital Episode Statistics, ICD-10: HES diagnostic codes, OPCS: HES procedure codes, S4N: Smart4NIPE national database, TSC: Trial Steering Committee.

Specialist examination of 140,000 babies for the study to determine “true” disease (cataract) status would be impractical. Therefore, bespoke data linkage with Hospital Episode Statistics (HES) records at least six months after birth will be used to identify registered babies who have subsequently received a specialist diagnosis of cataract (based on both diagnostic and procedure codes). This, with additional expert review of the images when required, will provide the gold standard evaluation of disease status.

All babies referred for specialist examination (either due to abnormal standard, digital imaging or both) will undergo expert review of the digital images by the Chief Investigator (CI).Babies with double negative (evaluated as normal screening tests) but HES evidence of diagnostic/procedure codes indicating cataract will have their digital images reviewed by two independent expert ophthalmologists drawn from the Trial Steering Committee (TSC). This will determine if there was evidence of cataract at birth (which should have been detected by screening) to the gold standard or whether the cataract developed subsequently.10% of all double negative eye images will be routinely reviewed by the CI for quality control purposes. For cases where an abnormality is suspected on image review, a specialty referral will be organised for the baby within two weeks.

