## Statistics and data analysis plan

### Statistical method

Given the rarity of cataract, and to maximise the data from eyes with cataract captured in the study, the abnormal eye will be selected as the index eye for data analysis where there is a unilateral abnormal screening result. Where the screening test is abnormal bilaterally, the right eye will be selected as the index eye.

A comparison of the relative sensitivity and specificity of the two tests will be possible using the counts of discordant pairs of screening tests, where one, and only one, of the neocam and standard test results within a baby are positive. Thus this relative comparison will be estimable in a short space of time for the recruited population using the expert image review as the gold standard. Hence much of the statistical inference can be performed before the long-term follow-up of the babies with both tests as negative.

For both the groups with and without congenital cataracts (as determined by the gold standard) the sensitivity and specificity, respectively, will be compared. McNemar’s test will provide a p-value, and a 2-sided 2.5% significance level used to account for the two contrasts. The absolute difference and odds ratios will also be estimated and provide with 95% confidence intervals. 

An estimate of the absolute values of, rather than differences between, sensitivity and specificity will be made following TSC expert review of the neocam images of babies with double negative screening tests in whom diagnostic and / or procedure codes indicating cataract were retrieved from HES on data linkage (since the cataract may have developed after birth). A detailed statistical analysis plan will be produced before the final database lock or before any interim analysis is performed.

Equivalent comparisons of sensitivity and specificity for each screening test will be made within ethnic groups and screener experience levels.

Quantitative comparison of the ease of the standard screening examination to the intervention will be analysed by screener questionnaire at the end of that staff member’s rotation on the maternity ward or at the end of the study recruitment period, whichever is sooner
^
12
^. Summary statistics reporting on the numerical or categorical questions will be provided.

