### Data monitoring committee (IDMEC)/trial steering committee (TSC)

As the inventor of the neocam device, the study lead has potential conflict of interest in the study. To eliminate this, the study leadership will be transferred to the co-lead on completion of the recruitment period. Given the lack of intervention risk and the absence of data analysis during the recruitment period, the NIHR has permitted a subset of independent members on the TSC to additionally fulfil the role of the IDMEC. The TSC comprises experts from the fields of paediatric ophthalmology, neonatology and statistics in addition to the study leads. The group will meet 6 monthly from the initiation of site training to ensure the study is running as planned.

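### The discordant-pair comparison takes disease status from the Chief Investigator's reading of the neocam image, and the stated remedy for the inventor's conflict does not clearly cover that reading

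*Protocol article*

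**What the plan says.** **Who reads.** The protocol article, under Acquisition of the gold-standard data, states that every baby referred because of an abnormal result on either test or both "will undergo expert review of the digital images by the Chief Investigator (CI"). Two independent ophthalmologists from the Trial Steering Committee are provided only for babies negative on both tests who later have HES cataract codes.

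**What the reading is for.** The same section defines the gold standard mainly by HES linkage at least six months after birth: "This, with additional expert review of the images when required, will provide the gold standard evaluation of disease status". Primary outcome measure agrees, listing data linkage with or without expert image review. Statistical method differs: the relative comparison on discordant pairs can be made early "using the expert image review as the gold standard". For discordant babies the CI's review is the only expert image review that the article describes.

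**The conflict.** The committee section says: "As the inventor of the neocam device, the study lead has potential conflict of interest in the study". The remedy follows: "To eliminate this, the study leadership will be transferred to the co-lead on completion of the recruitment period".

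**What a reader could see.** On the screener's neocam call, The intervention says: "This evaluation is stored in the image file name". Under Acquisition of the standard screening data, abnormal red-reflex results are entered in the study database once both tests are done. Prevention of result contamination deals with screeners only.

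**The concern.** McNemar's test for sensitivity uses only babies with cataract in whom exactly one test was positive. Whether such a baby counts as a cataract is therefore as important as the test results. For these babies Statistical method relies on an image review for which one reader is named, who may have an interest in the device and may see the screening results.

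The image being read is also the index test's own image. If neocam missed a cataract because it shows poorly on that image, an honest reader may also find no cataract there. The baby then leaves the sensitivity denominator, and a case that counted for the standard test disappears. This needs no bad faith, and it works in one direction, towards neocam.

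At stake is the primary sensitivity result, which the Dissemination section says will go to the UK National Screening Committee.

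**Working it through.** **1. The planned number reproduces.** Number of participants required gives sensitivities of 70% and 95%, 35% discordance, two-sided 2.5%, 90% power and 67 cataracts. The difference of 25 points and the total of 35% imply 30% neocam-only and 5% standard-only positives. Exact McNemar power, summed over the number of discordant pairs, is 89.9% at 66 cases and 90.4% at 67. The planned 67 is not in dispute.

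**2. Expected discordant cataracts.**
- At the planned 67: 0.35 × 67 = 23.5, split 0.30 × 67 = 20.1 and 0.05 × 67 = 3.4, about 20 v 3.
- At the abstract's prevalence of 1 in 3000: 140,000 / 3000 = 46.7, about 47. The split is 0.30 × 47 = 14.1 and 0.05 × 47 = 2.4, about 14 v 2.

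**3. Sensitivity of the p-value to single readings.** For b neocam-only and c standard-only cases with n = b + c and c < b, the exact two-sided p = 2 × P(X ≤ c), X ~ Binomial(n, 0.5).

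| Split | Basis | p |
|---|---|---|
| 14 v 2 | planning assumptions, 47 cases | 274/65,536 = 0.004 |
| 20 v 3 | planning assumptions, 67 cases | 4,096/8,388,608 = 0.0005 |
| 17 v 6 | assumed smaller difference, 23 pairs | 290,998/8,388,608 = 0.035 |
| 17 v 5 | as above, one standard-only case read as no cataract | 70,886/4,194,304 = 0.017 |

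The first two rows are already below 0.025, and losing standard-only cases only lowers p further. The 17 v 6 split is my assumption. It keeps 23 discordant pairs among 67 cataracts but corresponds to a difference of (17 − 6)/67 = 16 points instead of 25. There, one reading crosses the threshold.

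**4. False-positive rate if the tests are equally sensitive.** Assumptions, not from the article: 67 true cataracts, 35% discordant split 17.5% and 17.5%, and a fraction f of the standard-only cataracts read as no cataract. After that loss the neocam-only proportion is 0.175/(1 − 0.175f), the standard-only proportion is 0.175(1 − f)/(1 − 0.175f), and the number of cases is 67(1 − 0.175f), rounded. Rejection is by the asymptotic McNemar test at two-sided 2.5%. The last column repeats this with a 10%/10% split.

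| f | Cases left (17.5/17.5) | Rejection rate, 17.5/17.5 | Rejection rate, 10/10 |
|---|---|---|---|
| 0 | 67 | 2.3% | 2.3% |
| 10% | 66 | 2.7% | 2.5% |
| 20% | 65 | 4.0% | 3.3% |
| 30% | 63 | 6.6% | 4.7% |
| 50% | 61 | 18.3% | 10.6% |

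The inflation is small for f up to 20% and material from about 30%. The article gives nothing from which to estimate f. I have not sized the effect on specificity.

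**5. The remedy against the reading.** The handover takes effect when recruitment ends and concerns who leads the study. Nothing in that section addresses who reads the images of screen-positive babies, or what the reader can see.

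**The case against.** Several stronger statements are tempting, and the documents do not carry them.

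- **The inventor is the reader.** A reader might infer this, since the review of existing evidence and the committee section credit the device to the study lead and the gold-standard section names the CI. The article never says that they are the same person.
- **The reading takes place during recruitment.** No date is given. The two-week referral sentence most naturally belongs to the 10% quality-control review just before it, and screen-positive babies are described as already referred. The remark that the relative comparison will be available quickly points to early reading, but only indirectly. A reading after the handover might fall to the co-lead.
- **The reading is unmasked.** The article shows only that results are stored where a reader could see them. It is a condensed account, and masking may be set out in the full protocol or analysis plan.
- **The CI alone decides who has cataract.** HES linkage is part of the gold standard in two sections, and discordant babies are referred for specialist examination. A cataract read as absent could be contradicted by later codes. This is a real counterweight, but Statistical method sets it aside for the relative comparison.
- **A couple of readings would decide the trial.** One can pick counts that cross the threshold, such as 12 v 4 (p = 0.077) becoming 12 v 2 (p = 0.013). That split matches no stated assumption. On the protocol's own assumptions the conclusion is robust.

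Three things stand after these objections. The two descriptions of the gold standard do not agree. The only stated remedy does not mention the reference reading. The reference reading uses the index test's own image.

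**Conclusion.** The point holds in this limited form and should be fixed; confidence is moderate. As written, the relative comparison rests on a reference status taken from the neocam image, with one named reader who may have a declared interest and could know the screening results. The article's claim that the conflict is eliminated goes further than the remedy it describes.

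The direction of the possible bias is clear and favours neocam. Its size is not. It would leave the conclusion unchanged at the planned 25-point difference, and could reverse it near a 16-point difference with 23 discordant cataracts. If the tests are equally sensitive, the error rate rises from 2.3% to 6.6% when 30% of the standard-only cataracts are read as absent (17.5%/17.5% split). The conflict part depends on two inferences: that the CI is the study lead, and that reading precedes the handover. The mismatch between sections and the use of the index test's own image depend on neither.

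**What to change.** 1. Reconcile Statistical method with Primary outcome measure and Acquisition of the gold-standard data. For screen-positive babies, the primary comparison should take disease status from the specialist/HES diagnosis already being linked, not from the CI's image reading.
2. For any image review that still contributes to disease status, remove the evaluation from the file name and hide both screening results from the reader.
3. Keep the CI's review for image quality and referral, and state that it does not set the reference status in the primary analysis.
4. Amend the committee section so that it no longer says the conflict is eliminated, and state whether the CI is the study lead and when the images are read.

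**Cost.** The relative comparison must wait for HES linkage, at least six months after birth, so the advantage of an early result is lost. Otherwise the change needs a renaming step at export and some protocol wording. Sending discordant images to the two Trial Steering Committee readers instead is possible, but needs extra reader time, and the reference would still be read from the neocam image.

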### Number of participants required

From the Cambridge proof-of-concept pilot study using non-specialist screeners, the sensitivity is assumed to be 70% and 95% for red-reflex and digital imaging screening by non-specialist staff respectively. Hence the treatment effect is assumed to be a 25% difference. Power calculations need further assumptions regarding the joint distribution of the test within individual babies; we assume the maximum rate, 35%, of discordant tests consistent with these margins. A 2-sided hypothesis test (McNemar’s) at the 2.5% significance level will have 90% power if 67 babies are recruited with cataracts, necessitating recruitment of 140,000 newborns for screening.

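### The two readers who decide whether a cataract missed by both tests was present at birth are sent babies already coded with cataract, so hindsight can shift the absolute sensitivities, though not the McNemar comparison

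*Protocol article*

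**What the plan says.** The selection rule stands in the protocol article under Acquisition of the gold-standard data, after the data linkage figure: "Babies with double negative (evaluated as normal screening tests) but HES evidence of diagnostic/procedure codes indicating cataract will have their digital images reviewed". The same sentence names the readers, who come from the Trial Steering Committee (TSC): these babies "will have their digital images reviewed by two independent expert ophthalmologists drawn from the Trial Steering Committee (TSC". Of their reading the article says: "This will determine if there was evidence of cataract at birth". The alternative outcome is that the cataract developed later.

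The Statistical method section repeats the rule and hangs the absolute estimates on it. The absolute sensitivity and specificity "will be made following TSC expert review of the neocam images of babies with double negative screening tests" in whom cataract codes were found on linkage.

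Two nearby provisions do not change this. A 10% sample of all double-negative images is also reviewed, but by the Chief Investigator and for quality control. The safeguards under Prevention of result contamination concern the clinicians who do the two screening tests and what they share, not the image readers.

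**The concern.** The HES code already tells the readers that the child has cataract. What is left to them is a retrospective judgement of timing: was something visible in an image that a screener called normal? As TSC members they can be expected to know the selection rule. Removing codes or file names would therefore not mask them, because membership of the set gives the diagnosis away. A reader who knows the later diagnosis may see faint signs that would otherwise be passed over. With no image from an uncoded baby in the set, there is no way to tell how often these readers would call a sign in such an eye.

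Their answer fills the missed-by-both cell, which belongs to the denominator of both absolute sensitivities. The Primary objective is to estimate as well as compare sensitivity and specificity, and Dissemination says the findings go to the UK National Screening Committee.

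**Working it through.** **Inputs from Number of participants required.** Sensitivities: "the sensitivity is assumed to be 70% and 95% for red-reflex and digital imaging screening by non-specialist staff respectively". Discordance: "we assume the maximum rate, 35%, of discordant tests consistent with these margins". Size: the test "at the 2.5% significance level will have 90% power if 67 babies are recruited with cataracts", "necessitating recruitment of 140,000 newborns for screening".

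**1. The plan's own figure.** With discordance pd = 0.35 (0.30 neocam only, 0.05 red-reflex only) and difference d = 0.25:

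n = [z(0.9875)·√pd + z(0.90)·√(pd − d²)]² / d² = [2.241 × 0.592 + 1.282 × 0.536]² / 0.0625 = 64.8, so 65.

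At n = 67 the exact McNemar test has 90.4% power. The 67 is reproduced closely enough.

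**2. Double negatives implied by planning.** At 35% discordance the both-positive cell is 0.70 − 0.05 = 0.65, so the both-negative cell is 1 − 0.65 − 0.35 = 0. The plan therefore gives no expected number to adjudicate. At the minimum discordance of 25% the both-negative cell is 5%, or 0.05 × 67 = 3.35 babies.

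**3. Effect of the readers' calls.** Let k be the double negatives ruled present at birth. Absolute sensitivity = (cataracts positive on that test) / (cataracts positive on at least one test + k). The range of k is an assumption.

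Base of 67, all positive on at least one test; neocam positive 0.95 × 67 = 63.65, red-reflex positive 0.70 × 67 = 46.9:

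| k | neocam | red-reflex | difference (points) |
|---|---|---|---|
| 0 | 95.0% | 70.0% | 25.0 |
| 1 | 93.6% | 69.0% | 24.6 |
| 5 | 63.65/72 = 88.4% | 46.9/72 = 65.1% | 23.3 |
| 10 | 63.65/77 = 82.7% | 46.9/77 = 60.9% | 21.8 |

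That is about 1.2 to 1.4 points per baby for neocam and about 1 for red-reflex.

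Base of 140,000/3,000 = 46.7, using the abstract's prevalence; neocam positive 44.3, red-reflex positive 32.7:

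| k | neocam | red-reflex |
|---|---|---|
| 1 | 93.0% | 68.5% |
| 5 | 85.8% | 63.2% |
| 10 | 78.2% | 57.6% |

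The first baby costs about 2 and 1.5 points. The gap between 47 and 67 is a separate matter; both bases are shown so that the size does not rest on either.

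**4. What does not move.** McNemar's test uses only discordant pairs, so its counts and p-value do not depend on k. The ratio of sensitivities is 63.65/46.9 = 1.357 at every k. For specificity, moving ten babies out of about 140,000 − 67 = 139,933 non-cases changes it by at most 10/139,923, under 0.01 percentage points.

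**The case against.** **Silence in a condensed article.** The article names who needs adjudication but does not describe reading conditions, and masking or control images may be set out in a document not shown. That stands as a caution. The point, however, rests on a selection rule stated in two sections, not on silence about masking. Followed as written, the rule gives these two readers coded babies and nothing else.

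**The main comparison.** A reader might infer that the superiority test is compromised. The documents do not support this: double negatives do not enter the discordant counts.

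**The size.** A reader might take the introduction's figure, that only 60% of operated children under two were referred through screening, and conclude that up to 19 of 47 cataracts (0.4 × 47) could reach these readers. That does not follow. The figure describes referral of operated children, not babies negative on both tests, and nothing says their cataracts were visible at birth. At 95% neocam sensitivity, genuine double negatives cannot exceed 5% of cataracts, about 2.3 of 47 or 3.4 of 67. A k of five or ten would therefore have to consist mostly of later-onset cases called present at birth, and the documents do not say how many such babies there will be.

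**The direction.** A reader might also infer a known downward bias. Hindsight would plausibly raise the calls and lower both sensitivities, but the documents do not establish it. A true missed case added to the denominator is a correct result; only wrong calls are bias.

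**The remedy.** Uncoded images show how often readers call a sign in eyes without a cataract code, not in children whose cataract came later. They are also imprecise in small numbers: with no calls in 25 images the approximate upper 95% bound is 3/25 = 12%. This limits what the control call rate can show. It does not remove the benefit of masking.

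**Conclusion.** The point holds in a limited form. The reading set as stated reveals the later diagnosis to the readers whose decision fixes the missed-by-both count. What is exposed is the pair of absolute sensitivities, and the absolute difference if these babies are in its denominator.

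The tabulated shifts assume that 0 to 10 later-onset cases are wrongly called present at birth and that the planning sensitivities hold. They show the leverage of each call, not an expected error. The share of calls that hindsight would change is unknown, and the plan as written offers no means of measuring it. This is a worthwhile and inexpensive improvement to a secondary strand of the analysis, not a flaw in the hypothesis test.

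**What to change.** In Acquisition of the gold-standard data and in Statistical method, state that:

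- the same two TSC readers read the coded double-negative images in random order, mixed with stored images from double-negative babies without cataract codes, for example from the 10% quality-control sample;
- identifiers, HES status and the screener's evaluation are removed, and each reader calls every image independently before unmasking;
- the call rate in the uncoded images is reported, described as the false-call rate in eyes without a cataract code;
- absolute sensitivity is reported twice, counting cases called by both readers and cases called by either.

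The ratio of uncoded to coded images, and any matching by site or date, are optional.

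The cost is a few sentences and a modest number of extra stored images to read. No baby, reader or procedure is added, and sample size and power are unchanged. An occasional uncoded image may be called abnormal; the referral sentence already in that section would then apply. The article's Study status places the trial before site training, so the rule can be set before any image is read. Once readers have seen a coded-only set, masking cannot be restored for those images.
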